### Trial design {8}

The intervention part of the QFS-study consists of two designs. First, a RCT with concealed block randomization and 1:1 allocation ratio. Second, an exploratory single-subject experimental case series design for all participants (i.e., multiple *N*=1). Biological assessments will be completed at three out of four RCT study visits.

## Methods: participants, interventions, and outcomes

### Study setting {9}

The QFS-study will recruit 60 fatigued participants for the RCT (3 subgroups: QFS, CFS/ME, and JIA, each *N*=20), and up to 80 healthy controls for the biological objectives. Recruitment will take place at the Wilhelmina Children’s Hospital, part of the University Medical Centre Utrecht (UMCU) in Utrecht, The Netherlands.

### Eligibility criteria {10}

To be eligible, fatigued participants and healthy controls must be at least 12 years old and no older than 29 years during baseline. All must be able to speak, read, understand, and write Dutch. Fatigued participants must own a smartphone. Individuals with a diagnosis of chronic Q-fever and active disease are excluded from participation. Individuals are also excluded in case of cognitive impairment with an estimated IQ of below 70, or any concomitant (predominant psychiatric) diagnosis that can explain fatigue at baseline, such as major depressive disorder.

#### Additional criteria for participants with QFS

All 20 participants must enter the screening process with a (suspected) diagnosis of QFS according to the Dutch guidelines [25]. Participants must have suffered from debilitating fatigue with detrimental effects on daily functioning in work and/or private life for at least 6 months. The debilitating fatigue must have started before the age of 18, and after infection with *Coxiella burnetii*—where fatigue severity increased significantly after infection. All participants in the QFS group must be seropositive for *Coxiella burnetii* and cannot have a diagnosis of chronic Q-fever or recent diagnostics (< 3 months) demonstrating an IgG phase 1 titer of <1:1024 (or 1:512 in case of patients who are immunocompromised, or with a vascular prosthesis or a heart defect). At the time of screening, fatigue must be severe. This is indicated by a score higher than 39 on the Checklist Individual Strength-8 (CIS-8) questionnaire, which ranges from 0 to 56, with higher scores indicating more fatigue [26].

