### Sample size {14}

As described earlier, the QFS-study concerns a RCT with implemented *N*=1 design. The objectives of the study with *N*=1 design do not require a sample size calculation. Therefore, power analysis was performed for the group-level analyses on the primary outcome “fatigue severity”, which will be measured pre-post interventions. Based on previous CBT studies aiming to reduce chronic fatigue [18, 26], with an alpha of .05, power of .80, repeated measures correlation of .23, and an anticipated Cohen’s *f* effect size of .5, the sample size calculation for repeated measures 2 × 2 ANOVA yields *n*=16 per group. Taking into consideration an expected drop-out rate of 20% from previous single-subject experimental case research with multiple measurement on severe fatigue in adolescent patients with an immune dysregulation disorder, we will include 20 participants per group (i.e., QFS, CFS/ME, JIA), resulting in *N*=60. With *N*=60, it was decided upon expert medical and research lab opinion to include up to 80 healthy controls to increase the likelihood of recruiting healthy controls with seropositive *Coxiella burnetii* status, of observing contrasts in biological parameters, and to enable matching for age and gender as much as possible.

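### As worded, the QFS titre criterion excludes low recent IgG phase 1 titres and leaves high ones unrestricted, against its pairing with the chronic Q-fever exclusion and against its own exception

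*Protocol article*

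**What the plan says.** The protocol article sets the serological rule for the QFS group in Additional criteria for participants with QFS. It first requires antibodies: "All participants in the QFS group must be seropositive for" *Coxiella burnetii*. The same sentence then says that these participants cannot have either of two things: a chronic Q-fever diagnosis, or "recent diagnostics (< 3 months) demonstrating an IgG phase 1 titer of <1:1024". A parenthesis changes the cut-off for some patients: "or 1:512 in case of patients who are immunocompromised, or with a vascular prosthesis or a heart defect".

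Eligibility criteria {10} carries a related exclusion for everyone: "Individuals with a diagnosis of chronic Q-fever and active disease are excluded from participation". That exclusion is framed by diagnosis and gives no titre. No other section of the article restates the titre rule or corrects its direction.

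**The concern.** The titre limb sits beside a diagnosis of chronic Q-fever under one prohibition, so a reader expects both limbs to keep out the same kind of patient. Read literally, the titre limb removes seropositive candidates with low recent titres and places no upper limit on titre. The lower cut-off for a named subgroup then relaxes the rule for that subgroup, where the pairing suggests a tightening.

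The rule helps to define the QFS group. That group is 20 of the 60 planned trial participants (Study setting {9}), a randomisation stratum (Sequence generation {16a}) and the index group for the fourth objective, which compares biological profiles with CFS/ME, JIA and healthy controls (Objectives {7}). Some of the planned blood analyses use Q-fever seropositive and seronegative controls (the specimen section, item {33}). If the direction of the titre rule is unclear, so is the serological make-up of the index group in those comparisons.

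**Working it through.** The article gives no calculated figure on this point, so the check is one of logic.

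**Inputs, all from Additional criteria for participants with QFS**
- S: seropositive (required).
- A: diagnosis of chronic Q-fever.
- B: recent (under 3 months) IgG phase 1 titre below the cut-off.
- Cut-off: 1:1024, or 1:512 in the named subgroup. The parenthesis carries no sign of its own, so I take it to inherit the *less than* sign.

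**Step 1: the logical form.** The sentence reads: S and not (A or B). This equals S and not A and not B. A candidate with a recent titre below the cut-off is out; one at or above it is not barred by this clause.

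**Step 2: apply it** to a seropositive candidate with no chronic Q-fever diagnosis and a recent result, reading 1:2048 as a higher titre than 1:1024.

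| Recent titre | Other patients (cut-off 1:1024) | Named subgroup (cut-off 1:512) |
|---|---|---|
| 1:256 | excluded | excluded |
| 1:512 | excluded | not excluded |
| 1:1024 | not excluded | not excluded |
| 1:2048 | not excluded | not excluded |
| 1:4096 | not excluded | not excluded |

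Low titres are barred and high ones pass. The two columns differ only at 1:512, where the subgroup is treated more leniently.

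**Step 3: test the exception against the opposite direction.** This is a test of coherence and not a proposed rule. If the clause barred titres at or above the cut-off, 1:512 would exclude the subgroup and not others. If it barred only titres above the cut-off, 1:1024 would exclude the subgroup and not others. Either way the lower cut-off would be the tighter one. The exception therefore fits the pairing with chronic Q-fever only if the clause is meant to keep higher titres out, which is not what it says.

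**Step 4: the likely repairs are not equivalent.** The slip could be a reversed sign or a lost positive requirement (recent diagnostics must show a titre below the cut-off). Both would keep high titres out, but they differ for a candidate with no phase 1 result in the past 3 months. A reversed sign leaves that candidate eligible; a positive requirement does not. They can also differ for a result exactly at the cut-off. The article cannot settle which was meant.

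**The case against.** The strongest reply has five parts.

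1. *The diagnosis exclusion is intact.* This stands. A person with a recorded chronic Q-fever diagnosis is excluded by a separate limb of the same sentence, and Eligibility criteria {10} also excludes on diagnosis. A reader might infer that the wording admits the very patients whom the general exclusion is meant to keep out. The documents do not support that. What is lost is a further screen among people without a recorded diagnosis.

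2. *The intended direction is inferred.* This also stands. The article nowhere says that a high phase 1 titre marks chronic Q-fever, and it does not call the named subgroup higher-risk. The inference rests on the pairing of the two limbs and on the exception. It is strong enough to show that the parts pull apart, but not to say what the rule should be.

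3. *The sentence can be rescued.* Read as a positive requirement, the titre limb makes sense, but it needs a verb that the sentence lacks. Read as a fraction, 1:2048 is less than 1:1024, and the clause and its exception then agree. That is not the usual way to read a titre. An entry criterion whose sense depends on an unusual convention still needs rewording.

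4. *Other gates would catch misapplication.* Entry also requires a confirmed or suspected QFS diagnosis under the Dutch guidelines, and Recruitment {15} describes a uniform diagnostic work-up by specialists. This makes literal application unlikely, and the slip may be confined to the article. It lowers the probable impact without making the published criterion coherent.

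5. *The randomised comparison is untouched.* This stands. The criterion acts before allocation, and randomisation is stratified by patient group, so it bears on both arms alike.

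**Conclusion.** The clause is wrong as written. It bars low recent titres, sets no upper limit, and is looser for the named subgroup than for other patients. This rests on the usual ordering of titres and on the parenthesis inheriting the *less than* sign.

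The reach is narrower than it may first appear. Only people without a recorded chronic Q-fever diagnosis who have a phase 1 result from the past 3 months are affected. A reader might infer that all 20 QFS participants are affected, because the rule governs all of them. The article does not say that everyone has a recent phase 1 titre and reports no titre distribution, so the number could lie anywhere from 0 to 20 and cannot be narrowed. Nothing shows that anyone was wrongly enrolled or turned away.

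A reader might also infer harm to participants. The article shows no route to it: the interventions are lifestyle and dietary advice, and the study is described as minimal risk (item {11b}). What remains at stake is who makes up the QFS group and how the exploratory biological contrasts are interpreted. The PROfeel-versus-diet comparison is not biased.

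**What to change.** Reconcile the titre clause with the chronic Q-fever exclusion in Eligibility criteria {10}, with its own exception, and with protocol version 6, which Trial status names as the version described. State the direction of the inequality once, in a sentence separate from the prohibition. In the same place, say whether a recent phase 1 result is required or only disqualifying when present, and how a result exactly at the cut-off is treated. The sponsor must take the rule from the approved protocol; none is proposed here.

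Then check the recorded screening titres of enrolled QFS participants against the reconciled rule and report any that do not meet it. Trial status gives the start of recruitment as January 2021 and the approval of version 6 as March 25, 2021, so the check should note which protocol version applied at each screening.

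The cost is a short correction to the text and a review of at most 20 screening records if recruitment meets its target. Sample size, randomisation and the primary analysis do not change.

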#### Additional criteria for participants with CFS/ME

All 20 participants must enter the screening process with a (suspected) diagnosis of CFS/ME according to the Centers for Disease Control (CDC) criteria [1]. The biological trigger for CFS/ME can be unknown or diverse. Participants with SARS-COV-2 infection prior to CFS/ME diagnosis with CDC criteria are not excluded. Participants cannot have a QFS diagnosis. At the time of screening, fatigue must be severe (i.e., CIS-8 > 39).

#### Additional criteria for participants with JIA

All 20 participants must enter the screening process with a diagnosis of JIA. Participants must be on stable medication and have a stable disease activity score (Juvenile Arthritis Disease Activity Score; JADAS criteria) [27] for at least 3 months. Participants cannot have a QFS diagnosis. At the time of screening, the participant must express fatigue as a main complaint in the last 3 months. At the time of screening, fatigue must be severe (i.e., CIS-8 > 34, which indicates severe fatigue in JIA).

#### Additional criteria for healthy controls

Healthy controls must have no severe fatigue complaints (i.e., CIS-8 ≤ 39) and may either be seropositive or seronegative for *Coxiella burnetii* or SARS-COV-2. Serological status will be assessed after inclusion. Healthy controls are preferably siblings or friends of participating patients with QFS to increase the likelihood of recruiting healthy individuals with seropositive *Coxiella burnetii* status.

### Who will take informed consent? {26a}

The executive investigator will provide participants with oral and written information about the QFS-study, and obtain written informed consent from all participants before participation. In case participants are younger than 16 years, written informed consent will also be obtained from both parents or legal guardians before participation.

### Additional consent provisions for collection and use of participant data and biological specimens {26b}

Before participation in the study, the executive investigator will obtain written informed consent for the collection, storage and analysis of participant data, and biological specimens (i.e., blood, stool, saliva, and hair samples) from all participants. In case participants are younger than 16 years, written informed consent will also be obtained from both parents or legal guardians before participation.

## Interventions

### Explanation for the choice of comparators {6b}

The effectiveness of patient-tailored PROfeel lifestyle advices in reducing “fatigue severity” and improving “quality of life” and “self-efficacy” will be compared with generic dietary advices based on the Netherlands Nutrition Centre (NNC) (www.voedingscentrum.nl). The PROfeel method has previously been found feasible and useful by fatigued adolescents [23]. The next step is to test whether the patient-tailored PROfeel lifestyle advices are also effective in terms of reducing “fatigue severity”. Based on an established relationship between the gut microbiome and fatigue [28], a healthy diet is expected to positively influence the gut microbiome, potentially reducing fatigue. It has been shown before that nutritional advice can decrease some medically unresolved fatigue complaints in Dutch children [24].

### Intervention description {11a}

#### Patient-tailored PROfeel lifestyle advice

The RCT starts with a 4-week ESM assessment (see Table 1 for timeline). ESM is an innovative, validated, structured diary technique for longitudinal measurements of fluctuating states, that captures life as it is lived on the spot [22, 23, 29]. Multiple ESM applications are available for smartphones. In this study, we use the Ethica application (www.ethicadata.com) in which participants complete ESM surveys (i.e., diaries) approximately 5 times per day. In a first step, ESM data are used by a statistician to compute an individual descriptive report and an individual dynamic report with fatigue-perpetuating dynamic networks, identifying the contemporaneous and time-lag relations between fluctuations in fatigue and behavior, sleep, social context, cognitions, and feelings [23]. In a next step, the investigator uses the descriptive and dynamic reports to produce a reduced PROfeel report. Face-to-face, the investigator and participant discuss the PROfeel report and use shared decision-making to formulate a patient-tailored lifestyle advice. The term “lifestyle” here refers to an area of daily life that can be modified to potentially reduce fatigue and/or improve quality of life and self-efficacy. The combination of ESM with personalized feedback, leading to patient-tailored lifestyle advices, is named PROfeel. Details follow in the sections underneath.

**Table 1 Tab1:** Participant timeline in QFS-study

Week	Activity	Description
0	Screening	Evaluation of participant’s eligibility for the QFS-study by social pediatrician (and pediatric immunologist/rheumatologist in case of JIA diagnosis).
1	Study visit T0	Participant completes baseline KLIK questionnaires and installs the PROfeel app on smartphone to start ESM measurement. Participant also starts weekly measurement (of fatigue, quality of life, and self-efficacy) on smartphone which lasts throughout the study.
1-4	ESM phase I	Participant starts 4 weeks of ESM, with 5 surveys to answer per day. Surveys contain items inquiring after, e.g., fatigue and other symptoms, (social) activities, and affect in the last 3 h.
5	Study visit T1	Participant completes T1 KLIK questionnaires and is randomly allocated to either 12 weeks of patient-tailored PROfeel lifestyle advice or generic dietary advice. Biological samples (i.e., blood, stool, saliva, and hair) are collected for the first time.
5-16	Intervention I	Participant adheres to allocated advice for 12 weeks. To improve adherence, participant receives a boost from the investigator by phone and/or mail.
17	Study visit T2	Participant completes T2 KLIK questionnaires and evaluates first intervention with investigator. Biological samples (i.e., blood, stool, saliva, and hair) are collected for the second time.
17-20	ESM phase II	Participant starts a second period of 4 ESM weeks, with 5 surveys to answer per day. Survey items are identical to ESM phase I.
21	Study visit T3	Participant completes T3 KLIK questionnaires and is allocated to the other intervention arm (either 12 weeks of patient-tailored PROfeel lifestyle advice or generic dietary advice).
21-32	Intervention II	Participant adheres to allocated advice for 12 weeks. To improve adherence, participant receives a boost from the investigator by phone and/or mail.
33	Study visit T4	Participant completes T4 KLIK questionnaires and evaluates second intervention with investigator. If fatigue remains severe, participant can be referred to ECCF for post-trial care. Biological samples (i.e., blood, stool, saliva, and hair) are collected for the third time.
33-60	Follow-up	Weekly measurement (of fatigue, quality of life, and self-efficacy) on smartphone continues until 12 weeks after T4. During week 60, participant completes follow-up KLIK questionnaires, marking the end of QFS-study participation.

Healthy controls only have one study visit during which questionnaires (i.e., baseline KLIK, Eetscore, and optionally Food Frequency Questionnaire) and biological samples (i.e., blood, stool, saliva, and hair) are collected

*ESM* experience **s**ampling methodology, *CIS-8* Checklist Individual Strength-8 questionnaire, *ECCF* Dutch Expert Centre for Chronic Fatigue

#### PROfeel: ESM assessment

The ESM surveys are structured within the framework of the biopsychosocial model [16, 17], meaning that all surveys consist of a fixed set of items regarding potentially fatigue-perpetuating factors of biological, psychological, and social nature. These factors are part of the theoretical framework of efficacious elements of CBT [18]. Next to the fixed set, participants can add personalized items of their choice. These items represent additional somatic symptoms, symptom-related behaviors, feelings and cognitions, and a self-selected factor. This way, participants receive personalized surveys. Depending on the personalization, the surveys consist of 12 to 21 items. All items (e.g., “in the last 3 hours, I was fatigued”) are answered on a visual analogue scale (VAS) scale ranging from “not at all” to “very much”. Completing the personalized survey takes approximately 1 min. The ESM content was developed in an interdisciplinary team of researchers and clinicians and was previously tested in a feasibility study [23].

With regard to compliance, participants are asked to respond to at least 100 out of 140 ESM surveys (i.e., ≥70% compliance) to allow the computation of a reliable descriptive report and a reliable dynamic report with fatigue-perpetuating dynamic networks. PROfeel uses a time-based ESM recording method with interval contingency, meaning that all surveys are distributed at a fixed interval of 3 h. To allow for the highest compliance, participants are asked during the intake to select at what time slots they would like to receive their surveys (e.g., starting at 9 AM, 10 AM, or 11 AM each day).

#### PROfeel: feedback report and shared decision-making

After the ESM assessment, the investigator and statistician independently select which figures from the descriptive and dynamic reports should be discussed with the participant. This selection is based on statistical significance and relevance (i.e., weight and context of the dynamic network factor loadings, potential contribution to the patient’s self-knowledge, and usefulness as input for patient-tailored PROfeel lifestyle advice) and compiled into a PROfeel report. During a face-to-face meeting, the investigator discusses the PROfeel report with the participant. Input from the participant is leading for the interpretation of the figures. Participants are always asked to indicate the extent to which they recognize themselves in each figure. Two example figures are shown in the Additional files 1 and 2 (Figs. 1 and 2). Patients have considered the visual presentation of their symptoms a strong feature of PROfeel [23].

Once the PROfeel report is discussed, the investigator and participant decide what type of personalized lifestyle advice might help to reduce fatigue severity and/or improve quality of life and self-efficacy in daily life. This advice can be based directly on the figures from the PROfeel report, but may also be linked to something that came up during the meeting. Thus, the PROfeel report is used as a clinical conversation tool to create patient-tailored lifestyle advices. The report is not intended to be the sole input for lifestyle advices.

#### PROfeel: defining patient-tailored lifestyle advice

During shared decision-making, the investigator helps to define the lifestyle advice as feasible as possible. This is important since lifestyle advices often revolve around habits that need to be (re)learned. Because changing or learning habits is a slow process [30], the patient-tailored PROfeel lifestyle advices often represent a step in the participant’s process of (re)learning a habit. The advices incorporate factors known to strengthen habit learning, such as anticipating and avoiding self-control struggles, planning, and/or environment changes [30]. For example, when a participant struggles with rumination (i.e., worrying) throughout the day, an advice could be to reduce rumination time by practicing distracting attention. The investigator and participant could decide to work with a patient-tailored variation of “scheduled rumination” [31], in which the participant chooses a fixed timeslot to ruminate for 15 min, for instance, every day from 3:00 AM to 3:15 AM. To prevent self-control struggles, the participant and investigator compile a list of activities that help distract the participant from rumination. Whenever the participant finds him/herself ruminating outside the scheduled time, he/she is instructed to notice the thoughts, write them down if necessary, and divert attention with an activity on the list. Practicing scheduled rumination may lead to short-term improvement, provide insight in what the next step should be, and motivate the participant to take that next step in the long term.

Eventually, the patient-tailored PROfeel lifestyle advices will be adhered to for 12 weeks. During each week, the participant will receive a weekly survey on the Ethica app, inquiring about the levels of fatigue, quality of life, and self-efficacy in the past week, and whether he or she complied with the patient-tailored lifestyle advices.

